# The effects of oral hydrolytic enzymes and flavonoids on inflammatory markers and coagulation after marathon running: study protocol for a randomized, double-blind, placebo-controlled trial

**DOI:** 10.1186/2052-1847-6-8

**Published:** 2014-02-22

**Keywords:** Exercise, Inflammation, Upper respiratory tract illness, Oral hydrolytic enzymes, Flavonoids

## Abstract

**Background:**

Regular moderate intensity physical activity positively influences the immune system with a lower incidence of upper respiratory tract infections (URTI) and lower levels of pro-inflammatory markers. However, marathon running due to its strenuous and prolonged nature results in immune perturbations with a major increase in pro-inflammatory markers and subsequent increased incidence of URTI. Furthermore, marathon running results in muscle damage and changes in hemostasis that promote a pro-thrombotic state.

Naturally occurring hydrolytic enzymes and flavonoids have antioxidant, anti-inflammatory and fibrinolytic effects, and may serve as countermeasures to exercise-induced inflammation, immune dysfunction and URTI.

The aim of this study is to determine whether the ingestion of oral hydrolytic enzymes and flavonoids before and after a marathon attenuates post-race muscle damage and inflammation, counters pro-thrombotic changes in hemostasis and decreases URTI incidence.

**Methods/design:**

The Enzy-MagIC-study (**
*Enzy*
**mes, **
*Ma*
**rathon runnin**
*G*
**, **
*I*
**nflammation, **
*C*
**oagulation) is a randomized, double-blind, placebo-controlled, monocenter phase I trial. 160 healthy males (age 20-65 years) will be randomized to receive either placebo or treatment (Wobenzym, MUCOS Pharma, Berlin, Germany) which contains the hydrolytic enzymes (bromelain, trypsin) and the flavonoid rutoside. One week before the marathon race, participants will begin daily ingestion of the investigational product (3×4 tablets). Intake will be continued for two weeks after the race (3×2 tablets per day). Clinical and laboratory measures will be collected 5-weeks and 1-week before the race, and immediately-, 24-h, 72-h, and 2 weeks after the race. The primary endpoint is the influence of the treatment on the pre-to-post marathon race plasma concentration change of the inflammatory marker interleukin-6 (IL-6). Secondary endpoints include the effect of treatment on salivary IgA concentration and the frequency of upper respiratory tract infections (URTI) for two weeks post-marathon as determined by the Wisconsin Upper Respiratory Symptom Survey (WURSS-24). Furthermore, changes of muscular and rheological parameters will be measured before and after the marathon race.

**Discussion:**

We hypothesize that marathon-induced inflammatory perturbations and the incidence of subsequent URTI, muscular damage, and changes of hemostasis can be positively influenced by the anti-edematous, anti-inflammatory, antioxidant, and fibrinolytic effects of oral hydrolytic enzymes and flavonoids (Wobenzym).

**Trial registration:**

ClinicalTrials.gov Identifier: NCT01916408

## Background

Regular moderate intensity physical activity has been shown to positively influence the immune system [1,2]. Clinically this is represented by decreased incidence of upper respiratory tract infections (URTI) and pro-inflammatory markers in individuals who participate in regular moderate-intensity physical activity [2,3]. In contrast, most studies indicate that URTI rates increase during the 1-3 week period following marathon-type race events due to transient alterations in immunosurveillance [4-6]. Strenuous and prolonged exercise such as marathon running results in a major increase in inflammatory markers (e.g. C-reactive protein, interleukin 6) [6-8]. IL-6 is a cytokine with a wide range of biological effects, including pro-inflammatory influences during sepsis [9]. IL-6 is a central mediator of the acute-phase response and primary determinant of hepatic production of C-reactive protein (CRP) [10]. Elevated levels of IL-6 and CRP have been found in low-grade systemic inflammation such as atherosclerosis and diabetes mellitus [11,12]. In healthy men an elevated IL-6 plasma concentration has been associated with increased vascular risk and myocardial infarction [13]. IL-6 may stimulate blood coagulation and has been suggested to be an independent predictor for sudden death [14,15].

However, it is discussed equivocally whether IL-6 is primarily a pro- or anti-inflammatory cytokine. IL-6 activity appears to be essential for both the effective management of acute inflammation and to balance pro- and anti-inflammatory activity [16]. Post-exercise increases in plasma IL-6 are related to exercise workloads, with the highest levels found after strenuous and prolonged exercise [6-8]. Plasma IL-6 concentration decreases rapidly after strenuous exercise and is followed by increased levels of anti-inflammatory cytokines such as IL-1ra and IL-10 inducing an anti-inflammatory environment [2,17,18]. Chronic exercise, especially when accompanied with weight loss, is associated with decreased CRP and IL-6. This is linked to a reduced atherosclerosis and cardiovascular disease incidence [11,12].

Besides immune alterations, marathon running results in muscular damage which causes elevated levels of muscle enzymes (e.g. creatine kinase) and muscle soreness [19]. Additionally, changes of hemostasis leading to a pro-thrombotic state can be seen after a marathon race [20].

Consumption of plant derived foods such as vegetables and fruits has been linked to a reduced incidence of chronic diseases such as cancer and atherosclerosis [21,22]. The protective effects of these foods are attributed to hydrolytic enzymes and flavonoids that have antioxidant, anti-inflammatory, and anti-microbial effects [23-25]. The most important and therefore most extensive investigated flavonoids are rutosid (synonym rutin) and its glycosyl quercetin. Both flavonoids are mostly found in plants (such as apples) [26]. There are several studies investigating the antioxidant properties of these two flavonoids [26-30]. Whereas bromelain is a protein-digesting enzyme found in pineapple [31]. Nutritional supplements are being investigated as countermeasures to exercise-induced inflammation, immune dysfunction, and URTI [32]. Polyphenol-rich supplements under certain exercise conditions have been shown to exert anti-inflammatory and antioxidant effects [6,27,28].

Supplementation with oral hydrolytic enzymes has been reported to have analgetic, anti-edematous and anti-inflammatory influences [33,34]. Bromelain has the potential to decrease neutrophil migration and secretion of pro-inflammatory cytokines [25,35]. Furthermore, Bromelain reduces platelet aggregation and exhibits fibrinolytic activities in dissolving fibrin clots [31]. Trypsin has antioxidant effects, influences the activation of protease-activated receptor 2, and decreases the inflammatory response in animal models and in studies with allergic respiratory disease [36-38].

Wobenzym (brand name: Wobenzym® plus, Phlogenzym® or Wobenzym PS® depending on the country) is an orally applied formulation composed of hydrolytic enzymes (bromelain, trypsin) and the flavonoid rutoside. Clinical trials in both humans and animals suggest a beneficial effect of this combination on inflammatory diseases. These include immunologically mediated atherosclerosis in rat aortic allografts and rheumatologic disease [39,40]. Following injury, Wobenzym has been shown to restore microcirculation, decrease pain, reduce inflammation and swelling, and alleviate musculoskeletal symptoms to the same extent as nonsteroidal anti-inflammatory drugs [34,36].

Taken together, supplementation with polyphenols and hydrolytic enzymes appears to be a promising approach to mitigate marathon-induced changes in inflammation, muscular damage and soreness, and rheological status.

Therefore, the aim of the study is to investigate the influence of hydrolytic enzyme and flavonoid supplementation on changes in inflammatory, muscular, and rheological status in healthy males participating in a marathon race.

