**Figure 1 F1:**
[figure not shown]
**Study design and treatment schema of Enzy-MagIC-study (*****Enzy*****mes,*****Ma*****rathon runnin*****G*****, *****I*****nflammation,*****C*****oagulation-Study).** V1: visit 1 five weeks before marathon race. V2: visit 2 one week before race. V3: visit 3 immediately after race. V4: visit 4 one day after race. V5: visit 5 three days after race. V6: visit 6 two weeks after race. Red dots: study medication. One week before the marathon race, participants will begin daily ingestion of the study medication (3×4 tablets), with intake continued for two weeks after the race (3×2 tablets per day).

A total of 160 healthy male athletes between the ages of 20 and 65 years who intend to participate in the Munich Marathon 2013 will be recruited from August-September 2013. The inclusion and exclusion criteria are presented in Table 1.

**Table 1 T1:** In- and exclusion criteria for participants of the Enzy-MagIC-study

**Inclusion criteria**	**Exclusion criteria**
• Healthy* male	• Known cardiac disease
• Age 20-65 years	• Known allergy against the active ingredient of the study medication or pineapple, papaya, or kiwi
• History of at least one successfully finished half marathon	
• Intention to participate at the Munich Marathon 2013	• Known severe coagulopathy
• Subject is able to read, understand, and sign a written informed consent to participate in the Enzy-MagIC-study	• Known lactose intolerance
	• Pharmaceutical treatment for diabetes mellitus or arterial hypertension
	• Acute or chronic renal failure
	• Acute or chronic liver disease
	• Acute or chronic infection or inflammatory disease
	• Use of medications or supplements influencing immune function
	• Musculoskeletal or psychiatric disease
	• Neoplasia
	• Participation in other interventional trials

*Healthy means in accordance with the current WHO-definition a state of complex physical and mental well-being [41].

The study will be conducted in accordance with Good Clinical Practice guidelines, the guiding principles of the Declaration of Helsinki 2008, and local laws and regulations. The study protocol has been approved by the ethics committee of the University Hospital Klinikum rechts der Isar, Munich, Germany (approval reference number, 5820/13) and the Bundesinstitut für Arzneimittel und Medizinprodukte (BfArM), Bonn, Germany (Vorlagenummer, 4039219).

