### Interventions

One week before the marathon race, the participants will begin daily ingestion (oral use) of the investigational product Wobenzym (3×4 tablets) and for the two weeks after the marathon race 3×2 tablets. The treatment schema can be seen in Figure 1. Both Wobenzym dosages prior and after the race are in accordance with recommendations in the patient information sheet. In case of heavy inflammatory illnesses or after acute trauma, the dosage can be increased up to 12 tablets per day. Therefore, 12 tablets per day prior to the race should serve as a loading dose before the marathon race representing a inflammatory stimulus. After this loading period, the dosage is decreased to a maintenance dosage of 6 tablets per day. Based on this dosage regime, an adequate plasma concentration of rutoside, trypsin and bromelain can be expected in accordance to the study of Roots et al. [42].

The study product is Wobenzym, an orally applied enzyme-rutoside combination supplement. Each tablet contains 90 mg bromelain, 48 mg trypsin, and 100 mg rutoside. The current indications of the investigational product are swelling and inflammation caused by injuries/trauma, thrombophlebitis and inflammation of joints due to osteoarthritis. Pharmacological investigations in animals have proven no toxic, teratogenic or mutagenic characteristics after single, multiple or long-term intake.

Wobenzym (formerly known as Phlogenzym®) has been on the German market since 1991. Typical adverse reactions of this oral enzyme therapy are a change of consistency, color and odor of the stool. At higher doses, sensations of fullness, flatulence and diarrhea may appear. These symptoms may also be related to the excipient lactose. Very few allergic reactions have been reported. All reported adverse reactions have been minor and disappeared after discontinuation. None of the cases required further treatment. The placebo supplement for the control group consists of lactose-monohydrate and has no active ingredient.

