### Clinical measurements

Baseline data of the participants will be collected at the first visit. This includes questionnaires assessing training history, history of cardiovascular risk factors, physical examination, anthropometry, clinical chemistry, resting ECG, and echocardiography. One week prior to the race URTI-rates will be assessed daily by the Wisconsin Upper Respiratory Symptom Survey (WURSS-24) and will be compared between treatment and placebo group during the 2-week period following the race. The WURSS-24 is a reliable and valid tool for assessing symptoms, functional impairments, and global severity and global change of common cold [44]. Only complete questionnaires will be used for analyses.

Participants will be requested not to use medications influencing inflammation such as non-steroidal anti-inflammatory drugs. Furthermore, subjects will be asked to refrain from fatty food and from all polyphenol-containing foods, especially beverages such as wine, beer, and fruit juice, as well as fresh and dried fruits or vegetables. Nutritional intake will be recorded with a 3-days nutritional record before visit 2 and before the marathon race.

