### Statistical methods

The difference of logarithmized IL-6 values will be calculated for each participant as distribution of IL-6 differences within the groups is expected to be skewed. Differences of logarithmized values will be compared between both study groups using a two-sample t-test. A two-sided level of significance of 5% will be considered for this primary efficacy analysis. Quantitative secondary endpoints will be analyzed using ANOVA methods, and qualitative data using chi-squared tests. Analysis of the primary endpoint and the secondary efficacy endpoints will be performed following the intention-to-treat (ITT) principle. These endpoints will also be assessed in the per-protocol dataset in the sense of sensitivity analyses.

The ITT dataset will consist of all trial subjects enrolled into the trial and randomized. For subjects with missing post marathon inflammation markers, a conservative replacement of the missing values will be conducted by imputing the lowest observed post marathon value for the placebo group and the highest observed value for the treatment group. The per-protocol dataset includes all trial subjects who were treated according to protocol. A tertiary dataset for analysis is the safety population. This population includes all trial subjects who received any IMP or other trial treatment.

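### The primary IL-6 test is unadjusted, although the protocol ties the IL-6 rise to workload and collects training history at visit 1; a baseline covariate would add precision

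*Protocol article*

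**What the plan says.** **Outcome and workload.** The Background says that "Post-exercise increases in plasma IL-6 are related to exercise workloads, with the highest levels found after strenuous and prolonged exercise". It gives no slope or correlation.

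**Population.** Table 1 admits healthy men aged 20 to 65 with at least one completed half marathon.

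**Baseline data.** On the first visit, five weeks before the race, Clinical measurements says: "This includes questionnaires assessing training history". The article does not list the items in that questionnaire.

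**Primary analysis.** Statistical methods says: "Differences of logarithmized values will be compared between both study groups using a two-sample t-test". The analysis follows intention to treat, at a two-sided 5% level. No covariate is named.

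**Race data.** Laboratory measurements, Clinical measurements and Endpoints list no finish time, pace or race completion.

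**Tolerability.** Interventions says that "12 tablets per day prior to the race should serve as a loading dose before the marathon race" and that "At higher doses, sensations of fullness, flatulence and diarrhea may appear". The next sentence reads "These symptoms may also be related to the excipient lactose", and the same section says: "The placebo supplement for the control group consists of lactose-monohydrate and has no active ingredient". Table 1 excludes men with "Known lactose intolerance".

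**The concern.** The article treats exercise workload as a driver of its primary endpoint. In a field of this age range, with so low a bar for running experience, workload on race day may well vary a good deal between men. Part of that variation should be predictable from fitness and training before the race, and such information is collected. An unadjusted t-test leaves all of it in the error term. The cost is precision: wider confidence intervals and lower power than the same 160 men could give.

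A second, smaller matter concerns interpretation. The hypothesis credits the product with an anti-inflammatory action, and the Discussion says that it could become an alternative to NSAIDs if it proves efficacious. Randomisation balances prior fitness in expectation. It does not balance a change in running that the product itself might cause. Without finish time and completion by arm, a reader could not judge whether the two groups ran a comparable race.

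**Working it through.** **1. Reproduce the planned sample size.** Inputs from Sample size: CV 0.60, relative difference 25%, 80 per group, power 90%, two-sided alpha 0.05.

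- Log SD = √ln(1 + 0.60²) = √ln 1.36 = 0.5545.
- Difference = −ln 0.75 = 0.2877.
- Standard error = 0.5545 × √(2/80) = 0.0877.
- Noncentrality = 0.2877 / 0.0877 = 3.28. With 158 degrees of freedom, power is 90.3%.
- Required n is 79 per group by the normal approximation and 80 by the noncentral t.

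The stated 80 per group is therefore confirmed. Nothing below changes it.

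**2. Gain from a baseline covariate.** If the covariate explains a share R² of the variance of the log change, the residual SD is 0.5545 × √(1 − R²). The price is one degree of freedom (157 instead of 158). R² is an assumption, because the article gives none.

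| R² (assumed) | Residual SD | SE | Noncentrality | Power at 80 per arm | n per arm for 90% |
|---|---|---|---|---|---|
| 0 (t-test) | 0.5545 | 0.0877 | 3.28 | 90.3% | 80 |
| 0.1 | 0.5261 | 0.0832 | 3.46 | 93.0% | 72 |
| 0.2 | 0.4960 | 0.0784 | 3.67 | 95.4% | 64 |
| 0.3 | 0.4639 | 0.0734 | 3.92 | 97.4% | 56 |

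The confidence interval shortens by 1 − √(1 − R²), that is by about 5%, 11% and 16%. These figures are for complete data. Missing post-race values are to be replaced by extreme observed values, which are unrelated to the covariate and would reduce the gain.

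**3. How far a changed race could move the IL-6 contrast.** Let r be the correlation of race workload with the log IL-6 change, and d the difference in workload between the arms in SD units. Both are assumed. The shift is r × d × 0.5545. With no direct effect of the product:

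| r | d | Shift (log) | Apparent IL-6 reduction | Chance of a significant result |
|---|---|---|---|---|
| 0.3 | 0.1 | 0.0166 | 1.6% | 5.4% |
| 0.5 | 0.2 | 0.0555 | 5.4% | 9.6% |
| 0.5 | 0.5 | 0.1386 | 12.9% | 34.9% |
| 0.7 | 0.5 | 0.1941 | 17.6% | 59.5% |

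An observed difference that just reaches p = 0.05 is 1.975 × 0.0877 = 0.173, a ratio of 0.84. Workload alone would need r × d = 0.173 / 0.5545 = 0.31 to produce it. The full planned 25% would need 0.2877 / 0.5545 = 0.52. Small differences in running therefore matter little, and only a large one could pass for the planned effect. The last column is not a type I error rate for the effect of assignment, because a change in running caused by the product belongs to that effect.

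**The case against.** **A reader might infer that the primary test is confounded by slower running on the active product.** The article does not support this, for four reasons.

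- A change in running caused by the product is part of the total effect of assignment. The t-test remains unbiased and valid for that effect, and only the explanation of a difference is open.
- The article says that lactose may also cause the gut complaints, and the placebo is lactose. It gives no rates and describes the reported reactions as minor. An excess on the active product is possible but not shown, and nowhere does the article say that such complaints slow runners.
- The direction is uncertain. Over a fixed distance a slower race is less strenuous but more prolonged, and the Background names both features. The article also reports pain-relieving effects and expects less muscle damage, so treated men could run harder, which would mask a benefit.
- Dropping out does not simply favour the product. A treated man without a post-race sample receives the highest observed value, and a placebo man the lowest. Only a non-finisher who still gives blood could lower the active mean.

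**A reader might also infer that finish time goes unrecorded.** This is a condensed article, and the full protocol may provide for it. Only its absence from the article can be stated.

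**The remaining objection is that adjustment is a preference.** The CV of 0.60 was chosen for this population, and the power target is met without a covariate. That is correct: no error is shown. But the unadjusted test is a stated choice, and the article's own account of IL-6 gives reason to expect a gain from a better one.

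**Conclusion.** The point holds as an improvement in efficiency, with a modest addition for interpretation. Adjusting the primary model for one baseline performance or training measure would raise power from 90% to about 93 to 97%. This rests on the planning values in the article, on complete data, and on an assumed R² of 0.1 to 0.3. It also supposes that the visit 1 history contains a measure that predicts race workload and through it IL-6; the article ties IL-6 to workload but does not state this further link. If R² were near zero, adjustment would cost one degree of freedom and change almost nothing.

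A baseline covariate does not address a change in running caused by the product. Finish time and completion by arm would inform that question, in either direction. The unadjusted test is not biased for the total effect of assignment.

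**What to change.** 1. Replace the two-sample t-test with a linear model (ANCOVA) of the log IL-6 change on treatment and one prespecified measure from visit 1, such as best recent half-marathon time or weekly training volume. Keep the intention-to-treat set and the two-sided 5% level. Name the measure, its scale and the handling of missing covariate values before unblinding. Every participant must have finished a half marathon, so a time should exist. If visit 1 is over and no time was recorded, choose from the training items that were. Keep the unadjusted t-test as a sensitivity analysis.
2. Report official finish time and race completion (started, finished, distance if stopped) by arm as descriptive data.
3. Label any IL-6 analysis that adjusts for finish time, or is limited to finishers, as exploratory. Both condition on events after randomisation, so neither should be a condition for the primary conclusion.

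The cost is one covariate, one degree of freedom and one descriptive table. Finish times should be obtainable from the race organiser at little cost. The sample size need not change.

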## Methods

### Design and participants

Enzy-MagIC is a randomized, double-blind, placebo-controlled, monocenter phase I trial. Participants will be randomized in a 1:1 manner to receive either Wobenzym (treatment) or placebo. An overview of timing of randomization, treatment schema and data collection is presented in Figure 1.

